## Abstract

**Background:**

Out-of-hospital cardiac arrest (OHCA) remains a major cause of mortality, with low survival probabilities to hospital discharge. Despite the frequent use of airway management and mechanical ventilation during resuscitation, there is limited evidence regarding the optimal ventilation strategy to improve oxygen delivery and patient outcomes. The present study aims to investigate the effects of positive-end-expiratory-pressure (PEEP) set at 5 mbar compared to zero-end-expiratory-pressure (ZEEP) on the return of spontaneous-circulation (ROSC) in adult patients with OHCA.

**Methods:**

This is a prospective, multicenter, cluster-randomized controlled trial conducted across emergency medical services (EMS) in the regions of Gütersloh, Minden-Lübbecke, and Osnabrück. Adult patients (≥ 18 years) with OHCA who are undergoing mechanical ventilation through an airway device will be enrolled. The clusters (regional districts) will be randomized into two groups: one group will receive ventilation with PEEP set at 5 mbar (intervention group), while the other group will receive ventilation with ZEEP (control group). The study’s primary endpoint is the occurence of ROSC. Secondary endpoints include occurence of re-arrest, death during pre-hospital care phase, hospital admission during ongoing resuscitation, hospital admission with spontaneous circulation, peripheral oxygen saturation, and endtidal CO_2_ at hospital admission.

**Discussion:**

Optimal ventilation strategies during OHCA have not been well established. The use of PEEP may improve oxygenation and oxygen delivery. This study aims to provide crucial data on whether the application of PEEP at 5 mbar vs. 0 mbar can improve the probability of ROSC without adversely affecting hemodynamics. The findings could inform future guidelines on ventilation strategies in resuscitation.

**Trial registration:**

The trial is registered on ClinicalTrials.gov under the registration number NCT06836830. 24.02.2025 https://clinicaltrials.gov/study/NCT06836830?term=[name]&rank=2.

## Introduction

### Background and rationale {6a}

Out-of-hospital cardiac arrest (OHCA) occurs in approximately 67 to 170 individuals per 100,000 inhabitants annually across Europe, with survival to hospital discharge ranging from 8 to 18% [1]. Despite advances in resuscitation science, overall outcomes remain poor. Early, high-quality chest compressions and timely defibrillation remain key determinants of prognosis.

While the importance of optimal airway management during cardiopulmonary resuscitation (CPR) has been extensively studied and remains under debate, the evidence base for optimal ventilation strategies—particularly the application of positive end-expiratory pressure (PEEP) during CPR—is sparse.

In contrast, numerous studies in intensive care medicine (ICU) [2–4] have demonstrated that PEEP improves oxygenation, alveolar recruitment, and overall pulmonary mechanics [5–7]. However, the physiological conditions during cardiac arrest differ markedly from those in the ICU, especially with respect to circulation, intrathoracic pressures, and venous return.

Therefore, the transferability of established ICU findings to the resuscitation setting remains uncertain, and direct clinical evidence is limited [3, 4, 6, 8]. Investigating whether modest levels of PEEP during OHCA can improve oxygen delivery and alveolar recruitment without compromising hemodynamics is thus of high clinical relevance and may help bridge the gap between intensive care ventilation strategies and resuscitation practice.

Guidelines from the European Resuscitation Council provide general recommendations for ventilation during cardiac arrest but do not address the specific application of PEEP in this context [8]. Although every secured airway inevitably requires ventilation afterwards, there is little evidence supporting the best approach to ventilation after airway management.

Regarding whether manual ventilation using a bag-valve device or mechanical ventilation is more beneficial, there is currently limited evidence but many subjective opinions. Some individuals argue that having a tactile sense of lung compliance during manual ventilation can be advantageous, while other studies (e.g., from the Belgian Registry) suggest that mechanical ventilation after the insertion of an airway device might be beneficial. Despite these differing perspectives, there is still limited data on optimal ventilation settings.

For instance, one study demonstrated that a ventilation rate of 10 to 20 breaths per minute with controlled tidal volumes of 6 ml/kg and 100% oxygen during CPR resulted in ROSC in approximately 50% of cases, significantly higher than the usual ROSC probabilities of ≤ 30% [6].

As known from intensive care medicine PEEP can improve oxygenation by increasing functional residual capacity and recruiting collapsed alveoli, potentially benefiting patients undergoing CPR. However, PEEP may also reduce venous return and cardiac output, which could adversely affect the outcome. Therefore, determining the optimal PEEP level is critical in balancing the benefits of improved oxygenation against the risks of decreased cardiac output [8].

Existing studies have shown mixed results regarding the impact of PEEP during CPR. Animal studies have suggested that PEEP levels between 0 and 5 mbar may optimize the balance between oxygen delivery and hemodynamic stability. Specifically, a PEEP of 5 mbar was associated with the highest oxygen delivery and minimal adverse effects on cardiac output. However, PEEP levels above 10 mbar were shown to significantly reduce cardiac output [7].

The aim of the present study is to determine if a PEEP of 5 mbar during OHCA improves the likelihood of ROSC compared to ZEEP.

### Objectives {7}

The objective of the present study is to evaluate the effect of PEEP of 5 mbar vs. 0 mbar on the occurence of ROSC in OHCA.

### Trial design {8}

The study is designed as a prospective, cluster-randomized, multicenter interventional pilot trial. It employs a cluster-randomized design, where each participating EMS region in pre-defined time frames represents a cluster. The clusters will be randomly allocated to either the intervention group (receiving a PEEP of 5 mbar) or the control group (receiving ZEEP or 0 mbar) for a defined period of 6 months, followed by a crossover, where the same regions will switch to the opposite treatment arm for another 6 months.

The allocation ratio is 1:1 within each cluster, meaning that each group (intervention and control) will receive an equal number of patients. Since this is a pilot study, it is designed primarily to assess the feasibility and preliminary effects of the intervention rather than to definitively establish superiority. The results will provide the groundwork for future, more extensive studies.

## Methods: participants, interventions and outcomes

### Study setting {9}

The study will be conducted in pre-hospital EMS settings across multiple regions in Germany. Specifically, the study will involve EMS units from the following districts:GueterslohMinden-LuebbeckeOsnabrueck

With approximately 650,000 inhabitants across all regions combined. These EMS regions serve as the primary sites for data collection, and all resuscitation efforts in OHCA cases in these areas will be included. The study focuses on real-world pre-hospital settings where EMS teams provide critical care during cardiac arrest events before hospital admission.

### Eligibility criteria {10}

#### Inclusion

Adults ≥ 18 yearsNon-traumatic OHCAMechanical ventilation via airway device

#### Exclusion

Patients < 18 yearsTraumatic cause of OHCANo cardiac arrestWithholding of resuscitation (e.g., Do-not-Resuscitate orders).

### Additional considerations

Variables such as difficulty in airway management, timing of OHCA in relation to EMS arrival, and pregnancy will not serve as exclusion criteria.

These parameters are systematically documented in the standardized electronic case report form (eCRF) for every resuscitation case, allowing exploratory subgroup analyses to assess their potential influence on the primary outcome (ROSC).

Cases of clearly irreversible death (e.g., rigor mortis, decapitation, or other obvious signs of death) are not eligible for resuscitation and therefore not included in the study, in line with current resuscitation guidelines.

### Who will take informed consent? {26a}

Due to the nature of this study’s setting in a time-sensitive emergency situation and the current valuation of both treatment options, no consent is necessary. As every patient receives therapy in line with the guidelines, this was confirmed and approved by the ethics committee of the Ruhr-University Bochum (file reference 2024–1148) on 09.01.2024.

### Additional consent provisions for collection and use of participant data and biological specimens {26b}

Due to the nature of this study’s setting in a time-sensitive emergency situation and the current valuation of both treatment options, no consent is necessary. This was confirmed and approved by the ethics committee of the Ruhr-University Bochum (file reference 2024–1148) on 09.01.2024.

## Interventions

### Explanation for the choice of comparators {6b}

The choice of comparators in this study—namely PEEP at 5 mbar versus ZEEP at 0 mbar—is based on current gaps in clinical evidence regarding optimal ventilation strategies during OHCA. While mechanical ventilation during CPR is a critical component of patient care, there is limited data on the impact of varying levels of PEEP on outcomes such as ROSC.

PEEP has the potential to improve oxygenation by increasing functional residual capacity and recruiting collapsed alveoli, improving oxygen delivery to the tissues which could enhance the chances of ROSC [5]. However, higher levels of PEEP may also reduce venous return and subsequently cardiac output, which could be detrimental during resuscitation [7].

By comparing PEEP at 5 mbar (which animal studies suggest optimizes oxygen delivery without compromising hemodynamics) with ZEEP (the standard of care in many EMS settings), this study aims to determine whether the use of a modest level of PEEP can enhance resuscitation outcomes. Studies have indicated that a PEEP of 5 mbar may offer the best balance between oxygenation and maintaining cardiac output, which is crucial during resuscitation [7].

ZEEP was chosen as the comparator because it represents the baseline condition where no additional pressure is applied during the expiratory phase. This is a common practice in pre-hospital settings, where the main goal is to avoid excessive pressures that might negatively impact circulation [8]. Will the use of a moderate level of PEEP during resuscitation ultimately prove more effective compared to using ZEEP in improving patient outcomes during OHCA?

### Intervention description {11a}

The study will involve two groups of patients experiencing OHCA:PEEP Group (Intervention Group): Patients will receive mechanical ventilation with PEEP set at 5 mbar using the Medumat Transport ventilator, which includes an integrated PEEP valve allowing standardized settings. This aims to improve oxygenation during cardiopulmonary resuscitation (CPR).ZEEP Group (Control Group): Patients will receive mechanical ventilation with ZEEP (0 mbar) using the same ventilator model, representing the current standard practice in many EMS systems.

In the participating emergency medical services, PEEP application via manual bag-valve-mask ventilation is not intended and is not routinely performed in adult patients. Therefore, all PEEP interventions within this study are delivered exclusively via mechanical ventilation using the Medumat Transport device.

The specific ventilation settings (PEEP or ZEEP) are pre-assigned according to the cluster randomization and will be maintained throughout the resuscitation phase unless the treating physician deems a change clinically necessary.

### Criteria for discontinuing or modifying allocated interventions {11b}

The ventilation settings (PEEP or ZEEP) may be modified if the emergency team, based on their clinical judgment during the intervention, deems it necessary to make changes.

### Strategies to improve adherence to interventions {11c}

To ensure adherence to the intervention protocols, the following strategies will be implemented:Training and regular updates for all emergency medical personnel involved in the study.Standardized protocols for the use of ventilators and documentation of ventilation settings.Continuous monitoring and recording of ventilation parameters by the ventilator devices to ensure compliance.Periodic reviews of recorded data to identify and correct any deviations from the protocol.

These measures aim to maintain consistency across all trial sites and ensure adherence to the assigned interventions.

### Relevant concomitant care permitted or prohibited during the trial {11d}

All standard resuscitation measures according to current European Resuscitation Council (ERC) guidelines are permitted, including chest compressions, defibrillation, and administration of emergency medications (e.g., epinephrine, amiodarone, lidocaine).

After ROSC, ventilation management will follow standardized targets across both study groups to ensure consistency during the post-resuscitation phase:FiO₂ titration to maintain peripheral oxygen saturation (SpO₂) above 94%End-tidal CO₂ (ETCO₂) between 35 and 45 mmHgTidal volume of 6–8 mL/kg predicted body weight

The PEEP level will remain consistent with the group allocation throughout the post-ROSC phase—5 mbar in the intervention group and 0 mbar (ZEEP) in the control group—as documented in the eCRF.

This approach ensures uniform post-ROSC ventilation management while maintaining the integrity of the randomized intervention. All parameters are automatically recorded and subsequently extracted from the ventilator and eCRF for analysis.

### Provisions for post-trial care {30}

The study concludes upon the patient’s admission to the hospital.

### Outcomes {12}

Primary outcome:

The primary outcome is return of spontaneous circulation (ROSC), defined according to the Utstein template as the presence of a palpable carotid or femoral pulse during or after resuscitation, optionally confirmed by Doppler or ultrasound when available [9].

ROSC will be measured as a binary variable (yes/no), and the analysis will compare the proportion of patients achieving ROSC between the two study groups (PEEP vs. ZEEP).

This definition ensures consistency with international reporting standards and enhances the reliability of outcome assessment.

Secondary outcomes:oRe-Arrest-RateoDeath during pre-hospital care phaseoHospital admission during ongoing resuscitationoHospital admission with spontaneous circulationoSpO_2_ at hospital admissionoFiO_2_ at hospital admissionoetCO_2_ at hospital admissionOther outcomes:oDate of death (if applicable), analyzed as a time-to-event outcome, focusing on survival duration post-resuscitation.oDate of hospital discharge for survivors, measured as time to discharge.oNeurological status, measured as the Cerebral Performance Category at hospital discharge.

These outcomes are relevant as they provide a comprehensive assessment of both immediate and longer-term clinical effects of the interventions. ROSC is vital for short-term survival, while neurological status and vital signs reflect the quality of resuscitation and longer-term outcomes. Time to death and discharge further provide insight into survival and recovery rates.

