### Participant timeline {13}

#### Enrolment

*Time Point*: Patients will be enrolled *at the time of OHCA *(Fig. 1).*Inclusion Process*: Once a patient meets the inclusion criteria (OHCA, age ≥ 18 years, and undergoing mechanical ventilation), they will be immediately enrolled by the EMS team. The need for informed consent was waived by the responsible ethical committee.

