#### Interventions

PEEP or ZEEP Intervention:o*Time Point*: Immediately after advanced airway management is secured (using either an extraglottic airway device [EAD] or an endotracheal tube [ETT]).oThe assignment to PEEP or ZEEP is predetermined, as the defined time period dictates whether the patient will receive PEEP (5 mbar) or ZEEP (0 mbar). The sequence of these time periods has been randomized via cluster randomization.oThe intervention will continue throughout the resuscitation efforts until ROSC or cessation of resuscitation efforts.

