### Sample size {14}

The planned sample size is approximately 600 out-of-hospital cardiac arrest (OHCA) cases, with about 300 patients per group (PEEP vs. ZEEP).

The PerAVent trial is designed as a pilot and feasibility study, primarily aimed at evaluating the practical implementation of PEEP versus ZEEP ventilation in the pre-hospital setting and generating preliminary data for future confirmatory research.

The study hypothesis is that ventilation with PEEP (5 mbar) increases the probability of return of spontaneous circulation (ROSC) compared with ZEEP (0 mbar).

As this is a pilot study, no formal sample size calculation or power analysis has been performed, since no reliable prior data exist on which to base such assumptions. The chosen sample size is therefore based on feasibility considerations and expected case numbers within the participating emergency medical service regions over the planned study period.

The collected data will serve to estimate key parameters—such as recruitment rates, adherence, and effect size estimates—that may inform the design of a future confirmatory trial.

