## Data collection and management

### Plans for assessment and collection of outcomes {18a}

Data acquisition will be carried out using an eCRF, which is to be completed by the emergency care team following the resuscitation. The data collected will be supplemented with the ventilation parameters recorded by the emergency ventilators. The variables collected in the eCRF are shown in Table 1.

**Table 1 Tab1:** Variables collected in the eCRF

Category	Collected variables
Patient factors	Age (years), Sex, Comorbidities
Airway factors	Bag-mask ventilation before airway device placement (yes/no), Intubation (extraglottic airway device vs. endotracheal tube), Type of extraglottic airway device, Number of insertion attempts, Complications during insertion, Number of intubation attempts, Complications during intubation, Abandonment of intubation attempts, Re-intubation by emergency physician
Resuscitation data	Observed cardiac arrest (yes/no), Cardiac arrest observed by (layperson/emergency services), Layperson CPR performed (yes/no), Time to initiation of chest compressions, Resuscitation duration (minutes), Initial ECG findings, Defibrillation (yes/no), Number of defibrillations, Type of chest compressions (manual vs. mechanical), Type of mechanical compression device, Administration and cumulative dose of epinephrine and amiodarone
Intra-arrest ventilation data	Ventilation parameters set by emergency services (Pmax, PEEP, respiratory rate, tidal volume, inspiration-expiration ratio, FiO_2_, Ventilation mode: IPPV, BILevel, CCSV, Other), Ventilation parameters measured by Medumat Transport, Changes in ventilation parameters during resuscitation
Post-arrest treatment	Re-intubation from extraglottic airway to endotracheal tube (yes/no), Number of intubation attempts, Type and dose of analgesic, hypnotic, muscle relaxant, Complications in pre-hospital post-arrest phase (aspiration, ventilation issues, hypotension, re-arrest), Administration of catecholamines, Post-arrest ventilation settings
Additional outcome data	Consciousness at handover, ECG findings at handover, Glasgow Coma Scale, Vital parameters at handover (systolic blood pressure, heart rate, oxygen saturation, respiratory rate, etCO_2_), Initial blood gas analysis, Date of death, Hospital discharge date

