### Additional statistical considerations

All analyses will be conducted on an intention-to-treat basis. Exploratory subgroup analyses are planned to evaluate potential effect modifications, including presumed etiology of OHCA (respiratory/asphyxial vs. primary cardiac) and airway management difficulty. These analyses will be hypothesis-generating and interpreted with caution.

The study hypothesis is that ventilation with PEEP (5 mbar) increases the probability of ROSC compared with ZEEP (0 mbar).

No interim analyses are planned.

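### Entry and the primary outcome are not tied to ventilator connection, so a ROSC that precedes any PEEP or ZEEP can be counted as a primary success

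*Protocol article*

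**What the plan says.** All references are to the protocol article.

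- **Entry.** Eligibility criteria {10} require an adult with a non-traumatic OHCA who is mechanically ventilated through an airway device. The Enrolment section repeats the trigger: "OHCA, age ≥ 18 years, and undergoing mechanical ventilation), they will be immediately enrolled". Neither states that arrest must be ongoing when the ventilator is connected.
- **Start of the intervention.** The Interventions part of the participant timeline gives it as "Immediately after advanced airway management is secured". Intervention description {11a} adds that PEEP is delivered only by the ventilator, so there is no allocated exposure before connection.
- **After ROSC.** Relevant concomitant care {11d} states: "The PEEP level will remain consistent with the group allocation throughout the post-ROSC phase".
- **Primary outcome.** Outcomes {12} define ROSC as "the presence of a palpable carotid or femoral pulse during or after resuscitation", recorded yes/no, and "the analysis will compare the proportion of patients achieving ROSC between the two study groups (PEEP vs. ZEEP").
- **Analysis set.** Additional statistical considerations: "All analyses will be conducted on an intention-to-treat basis". There is no restriction to patients still at risk of the outcome at connection.
- **Data.** Table 1 covers the phase before the airway device with the item "Bag-mask ventilation before airway device placement (yes/no"). It lists no clock time of first ROSC.

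**The concern.** Chest compressions, defibrillation and bag-mask ventilation can all come before a secured airway. Some patients may therefore regain a pulse before the ventilator is attached and then be intubated and ventilated. On the stated criteria such a patient can enter the trial, receive the allocated setting under {11d} and score ROSC = yes. PEEP or ZEEP cannot have contributed to that ROSC.

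Two things are at stake. If these patients are equally common in both arms, they add successes that carry no information on the intervention and pull the difference towards zero. If they are not equally common, they bias the comparison in a direction that cannot be known in advance. The second is possible because crews know the allocation (Who will be blinded {17a}; the Discussion mentions stickers on the ventilators), and connecting the ventilator after ROSC is itself what makes such a patient eligible.

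The pilot label does not remove the problem. Sample size {14} says the data are to supply effect size estimates for a later confirmatory trial.

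**Working it through.** **The plan's own figures.** Sample size {14} gives about 600 cases, "with about 300 patients per group (PEEP vs. ZEEP"); 300 + 300 = 600 agrees. It states no alpha, power or effect, so there is no power figure to reproduce.

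**Inputs.**
- ROSC among patients still in arrest under ZEEP, p0 = 30%. The Background gives the usual ROSC probability as at most 30%.
- ROSC among patients still in arrest under PEEP, p1 = 40%. This is an assumption.
- Share of each arm with ROSC before connection, q. The document does not give it; the range 0 to 30% is an assumption.

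**Equal shares.** Observed proportion in an arm = q + (1 − q)p. Subtracting the arms gives an observed difference of (1 − q)(p1 − p0).

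| q | ZEEP | PEEP | Difference | Odds ratio |
|---|---|---|---|---|
| 0 | 30% | 40% | 10 points | 1.56 |
| 10% | 37% | 46% | 9 points | 1.45 |
| 20% | 44% | 52% | 8 points | 1.38 |
| 30% | 51% | 58% | 7 points | 1.33 |

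For q = 20%: 0.20 + 0.80 × 0.30 = 0.44 and 0.20 + 0.80 × 0.40 = 0.52. The odds ratio is (0.52/0.48)/(0.44/0.56) = 1.38.

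**Unequal shares.** Let the share be 20% in one arm and 10% in the other.
- No true effect (30% in both arms): 0.44 − 0.37 = 0.07, a spurious 7 points in favour of whichever arm has the larger share.
- True 10 points, larger share under ZEEP: 0.46 − 0.44 = 2 points.
- True 10 points, larger share under PEEP: 0.52 − 0.37 = 15 points.

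**Precision, for illustration only** (two-sided 5%, two-proportion normal approximation, clustering ignored).
- 300 per arm: power is 73% at q = 0 and 50% at q = 20%.
- Restricting the q = 20% case to the 300 × 0.80 = 240 per arm still in arrest (30% against 40%): power is 63%, despite the smaller number.
- Sizing a later trial at 80% power: 356 per arm from 30% against 40%, but 612 per arm from the diluted 44% against 52%.

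**The case against.** The strongest reply is that the protocol, read as a whole, describes ventilation during arrest. Enrolment is placed at the time of the arrest. Absence of cardiac arrest is an exclusion. Intervention description {11a} holds the setting through the resuscitation phase. The participant timeline ends the intervention at ROSC or when resuscitation stops. On that reading, {11d} merely continues a setting already in use. This stands as evidence of intent, and a reader who inferred that nothing in the document points to ongoing arrest, or that the design deliberately admits post-ROSC patients, would go too far. But the exclusion carries no time point and most naturally removes people who never arrested. The other passages describe treatment and limit neither entry nor outcome.

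A second reply is that earlier ROSC could be identified anyway. Table 1 separates intra-arrest from post-arrest ventilation data and records resuscitation duration, and the ventilators are read out. This partly stands: many such patients could probably be found. It does not help while the stated outcome and analysis set still count them.

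A third reply is that analysis-set detail belongs in an analysis plan that is not shown. Eligibility, the start of the intervention and the primary outcome are, however, fixed here, and the gap lies in how they fit together.

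Finally, the size rests on assumptions and the pilot claims no power. That stands in full.

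**Conclusion.** The point holds as a gap between three stated definitions. Entry and the primary outcome do not expressly require ongoing arrest at connection or ROSC after it, although intra-arrest ventilation appears to have been intended.

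The shrinkage factor (1 − q) is exact when q is equal across arms. Its size is unknown because the document does not give q; at an assumed 10% to 30%, a 10-point difference becomes 9 to 7 points. With unequal shares the bias can go either way, so dilution is a conditional result and not an established one.

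A reader might infer from the power figures that the trial is underpowered for its aim. The document does not support that: Sample size {14} makes no power claim, the 40% rate is assumed, and the figures ignore clustering by region. The practical harm is to the effect estimate meant to inform the next trial. The point should be settled before analysis.

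**What to change.** Before analysis:

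1. Define the primary analysis set as patients in cardiac arrest at first ventilator connection, and the primary outcome as first ROSC after that time.
2. Record the time of first ROSC and take connection time from the ventilator read-out. Record arrest status at connection as well, because the time of first ROSC alone does not classify a patient who re-arrested before connection.
3. For patients already enrolled, recover these items where possible from the EMS documentation, the ventilator read-outs and the intra-arrest and post-arrest ventilation fields.
4. Report patients with ROSC before connection separately by arm, which also shows whether the shares differ. Keep the all-enrolled analysis as a sensitivity analysis.
5. Reconcile {11d}, which keeps the allocated setting after ROSC, with the participant timeline, which ends the intervention at ROSC.

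Cost: an eCRF addition, wording in the analysis plan, and some retrospective work, since Trial status gives recruitment as June 1, 2025 to May 31, 2026 and still ongoing. The analysed number will be smaller than the enrolled number. Some selection remains, because unblinded crews still choose when to connect the ventilator; the restriction reduces that problem and does not remove it.

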### Assessments

During resuscitation:oContinuous monitoring of vital signs (e.g., HR, SpO_2_) and ventilation parameters (e.g., PEEP, tidal volume, etCO_2_).Post-resuscitation:o*Time Point*: Immediately upon achieving ROSC until handover at the hospital.o*Measurements*: GCS, vital signs (HR, SpO_2_), and optional initial blood gas analysis will be assessed.Follow-up assessments:o*Time Point*: During hospital stay, including assessments of neurological outcomes and cardiac function (e.g., EKG, vital signs) if applicable.o*Final Assessment*: Date of death (if applicable) or hospital discharge.

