### Visits for participants

No formal follow-up visits are required post-resuscitation as all data will be collected during the pre-hospital and hospital phases. The study focuses on immediate outcomes following OHCA and does not include long-term follow-up.

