## Statistical methods

### Statistical methods for primary and secondary outcomes {20a}

For the primary outcome (ROSC), a mixed logistic regression model will be used to analyze the difference in the probability of achieving ROSC between the two groups (PEEP vs. ZEEP). This model will account for the cluster-randomized design, adjusting for potential correlations within clusters (EMS regions).

For secondary outcomes, such as re-arrest rate, death during pre-hospital care, hospital admission during ongoing resuscitation, hospital admission with spontaneous circulation, SpO₂, FiO₂, and etCO₂ at hospital admission, linear regression models will be used for continuous variables, while logistic regression will be applied for binary outcomes (e.g., shockable vs. non-shockable rhythms).

The models will include relevant covariates, such as age, comorbidities, and other baseline characteristics, to adjust for potential confounders. Random effects will be included to account for variability between EMS regions.

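### Time to death is planned as a survival-duration outcome, but observation ends at hospital discharge, so it cannot be observed for patients discharged alive and the handling of live discharge must be defined

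*Protocol article*

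**What the plan says.** All references are to the protocol article.

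- **Outcomes {12}.** Under other outcomes, date of death is to be "analyzed as a time-to-event outcome, focusing on survival duration post-resuscitation". Time to hospital discharge is a separate outcome, restricted to survivors.
- **Assessments.** The final assessment is "Date of death (if applicable) or hospital discharge".
- **Visits for participants.** The article states that "all data will be collected during the pre-hospital and hospital phases", and that the study "does not include long-term follow-up".
- **Table 1 in {18a}.** The late outcome fields are "Date of death, Hospital discharge date". No vital status after discharge is listed.
- **Statistical methods {20a}.** Besides the mixed logistic model for ROSC, "linear regression models will be used for continuous variables, while logistic regression will be applied for binary outcomes". No time-to-event method, censoring rule or time horizon is given.
- **Provisions for post-trial care {30}.** "The study concludes upon the patient’s admission to the hospital". This conflicts with the outcomes and assessments that run through the hospital stay.

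**The concern.** A survival-duration outcome needs vital status beyond the moment a patient does well enough to go home. Here observation stops at exactly that moment. A patient who dies in hospital has a survival time. A patient discharged alive has only a length of stay.

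Live discharge is not a neutral exit. Discharged patients have a much lower hazard of death than those still in hospital. A default survival analysis (Kaplan-Meier, log-rank, Cox) that censors them at discharge assumes they go on dying at the inpatient rate. The resulting curve is neither in-hospital mortality nor survival, and its tail rests on a few long-stay patients. The excess depends on how many patients are discharged and how early, so it can differ by arm.

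Analysing time to discharge among survivors only is the other half of the same problem. It conditions on the event that competes with discharge, and survivors are a group formed after allocation.

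The stake is limited but real. {12} presents time to death and discharge as informing survival and recovery, and the sample size section {14} says the data may inform a confirmatory trial.

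**Working it through.** **Step 1: no figure to reproduce.** The protocol gives no event count, hazard ratio, horizon or power for this outcome. The check is therefore what censoring at discharge would do if it were used.

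**Step 2: inputs.**

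- From the protocol: about 300 patients per group ({14}); survival to discharge s = 8% to 18%, with midpoint 13% (Background {6a}); ROSC 30% to 50% (same section), used as a proxy for the share a admitted alive.
- Assumed, because the protocol does not give them: time to in-hospital death is lognormal with median 2, 3 or 5 days (sigma 1.2); time to live discharge is lognormal with median 15 or 20 days (sigma 0.6). The pairs used are 3/15, 5/20 and 2/15. Horizons are days 30 and 60. Pre-hospital deaths fall at time zero.

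**Step 3: formulas.** Let F_D and F_L be the distribution functions of time to in-hospital death and to live discharge, and f_D the density of the former.

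- Actual in-hospital mortality by day t: (1 − a) + (a − s)·F_D(t)
- Share still at risk: R(t) = (a − s)(1 − F_D(t)) + s(1 − F_L(t))
- Expected 1 − Kaplan-Meier with discharge censored: 1 − a·exp(−∫₀ᵗ (a − s) f_D(u)/R(u) du)

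**Step 4: one case in full (s = 13%, a = 50%, medians 3 and 15 days).**

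- F_D(60) = Φ(ln(60/3)/1.2) = Φ(2.496) = 0.9937, so actual mortality is 0.50 + 0.37 × 0.9937 = 86.77%.
- The integral to day 60 is 2.348, so 1 − KM = 1 − 0.50 × exp(−2.348) = 95.22%.
- The excess is 95.22 − 86.77 = 8.45 points. At day 30 it is 90.05 − 85.98 = 4.07 points.
- F_L(60) = Φ(ln(60/15)/0.6) = 0.9896, so R(60) = 0.37 × 0.0063 + 0.13 × 0.0104 = 0.0037. That is about one patient of 300 still at risk.

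**Step 5: range over all 18 combinations of s, a and timing.**

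| Curve | Excess at day 30 | Excess at day 60 |
|---|---|---|
| All enrolled | 1.4 to 4.4 points | 3.5 to 10.0 points |
| Started at ROSC | 4.5 to 8.8 points | 10.1 to 20.9 points |

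A separate simulation with other assumed timing (median death 3 or 5 days, sigma 1.1; median discharge 14 or 21 days, sigma 0.6) gave 0.7 to 6.3 points at day 30 and 1.7 to 12.3 points at day 60 in all enrolled patients. The direction was upward in every combination; the size moves with the timing.

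**Step 6: the arm comparison.** The bias in the arm difference is the difference between the two arms' excesses.

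- *Survival differs, timing equal.* The contrasts were 13 vs 16%, 13 vs 18% and 8 vs 13%, over the same ROSC shares and timings. The largest bias is for 8 vs 13% with a = 50% and medians 3/15: 4.07 − 3.20 = 0.87 points at day 30 and 8.45 − 5.96 = 2.49 points at day 60. The binomial standard errors of the difference are about 2.6 and 2.5 points, ignoring clustering. For the two contrasts starting from 13%, the bias is at most 0.4 points at day 30 and 1.5 points at day 60, and its sign varies.
- *Only length of stay differs.* With s = 13% and a = 50% in both arms, and median discharge at 15 vs 12 days, actual mortality is 86.8% in both. At day 60, 1 − KM reads 95.2% vs 97.1%, so faster discharge alone looks like 1.9 points more mortality.
- *Nothing differs.* The bias in the difference is zero.

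**The case against.** The strongest reply is that the faulty analysis is not in the document. No section names Kaplan-Meier, Cox or censoring at discharge. A cumulative incidence analysis with competing events is itself a time-to-event analysis, and both dates it needs are in Table 1. The estimator for an outcome outside the primary and secondary set is ordinary content for an analysis plan that is not shown, and {20a} covers only primary and secondary outcomes.

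Most of this stands. A reader might infer that the protocol commits to censoring at discharge and will therefore overstate mortality; the text does not support that. A reader might also infer that the treatment comparison is seriously distorted. The calculations do not support that in general: with equal length of stay the bias is below one point at day 30, and at day 60 it reaches about one standard error only in the most extreme case tried. Nor do the sizes come from the protocol, since the timing and horizons are assumed.

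What the reply does not answer is the mismatch between outcome and follow-up, because both are fixed in the article. An analysis plan can choose an estimator, but it cannot supply survival after discharge that nobody records. It can only redefine the outcome, which is the change asked for here.

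**Conclusion.** The point holds in conditional form. The protocol fixes survival duration as the outcome and discharge as the end of observation, and these do not fit together. The bias arises only if live discharge is then treated as ordinary censoring. In that case 1 − KM exceeds in-hospital mortality by about 1 to 4 points at day 30 and 3.5 to 10 points at day 60 in all enrolled patients, and by more if the curve starts at ROSC.

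These sizes rest on the assumed lognormal timing and on ROSC as a proxy for admission alive. They are measured against in-hospital mortality; any deaths after discharge would narrow the gap to true mortality.

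This is an other outcome in a pilot without a power calculation, and neither the ROSC analysis nor the secondary outcomes are touched. It should be corrected, but it does not threaten the trial's main result.

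**What to change.** - **Outcome.** In {12}, replace the survival-duration outcome with death before hospital discharge (yes/no) in all enrolled patients, counting pre-hospital deaths as events. Analyse it with the same mixed logistic model as ROSC.
- **If a time scale is kept.** Start it at a point common to all patients, such as the start of EMS resuscitation, because a curve started at ROSC selects patients on the primary outcome. Report the cumulative incidence of death by arm with live discharge as a competing event (Aalen-Johansen). Report discharge in the same way, instead of among survivors only.
- **End of study.** Reconcile {30}, which ends the study at hospital admission, with {12}, Assessments and Visits for participants. If {30} applied literally, in-hospital death could not be collected either.

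The cost is a sentence or two in {12} and the analysis plan. It uses dates already in Table 1 and needs no new patients or data. The downside is that the result describes in-hospital death, not survival duration. Keeping survival duration would instead require collecting vital status to a fixed day.
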